#### All Surveys

At each follow-up point, participants will receive an email invitation through REDCap to complete each of the surveys. A combination of text and email reminders (up to 5) to complete each survey will be sent every 24-48 hours to any participants who have not yet completed them. This is fewer than Dillman et al’s [40] recommended number (7 reminders), but we have found 5 sufficient to maximize survey completion rates. Participants are reminded of the study structure and reconsented at 6- and 12-month time points via an introductory page to the survey before progressing to the questions.

At the end of the postintervention and 6-month surveys, participants are asked to provide updated, detailed contact information (primary and secondary cell phone numbers and email addresses) so that we can contact them for subsequent follow-ups. For use in the event that an email or text is unable to be delivered, we will ask for (1) permission to contact the Registrar’s Office in case the contact information they have provided us is out of date and (2) contact information for 2 people who would know how to get in touch with them in case they have not updated their contact information with the Registrar. If text messages or emails are undeliverable at the 6- or 12-month surveys, we will ask the Registrar or the provided contacts for updated contact information only for those participants who have given us permission to do this. If we reach out to the participants’ nominated contacts, we will not share any information about the research study when we do so. We will only ask these individuals to ask the participant to contact us for those participants who have given us permission to do this.

### Incentives

In the second year of recruitment, the incentive for the 20- to 30-minute screening interview was increased from $5 to $10, based on attrition between preliminary screening/matching and the interviews. This change is reflected in the description of incentives that follows. For participation in this research, participants receive incentives (preloaded gift cards) of up to $105 or receive up to $70 and 2.5 course bonus points for those recruited from Participant Pools. Specifically, nonpool participants receive $35 for completing the screening interview, baseline, and 1-week postintervention surveys ($20 for screening and baseline alone if they do not complete both surveys), $30 for the 6-month survey, and $40 for the 12-month surveys. Pool participants receive 2.5 bonus points for completing the screening interview, baseline, and postintervention surveys (combined) which occur in the same semester in which they are registered for the participant pool (1.5 pts if they do not complete both surveys), and the same monetary incentives as nonpool participants for the remaining 2 follow-up surveys (which occur outside of that semester).

For each session attended and postsession evaluation completed, participants (in both trial arms) are entered into a postsession raffle for two $25 draws among the people who attended their session that day (max 16 participants). Participants assigned to IDEA^3^ are therefore eligible for up to $100 in session-end raffles (depending on how many sessions they attend) compared with $25 for control group participants, to compensate them for the longer time commitment involved. Further, for each intervention session attended, all participants (in both trial arms) receive a ballot for an end-of-term $250 raffle at each site.

Increasing incentives for each survey completed encourage students to stay in the trial for its full duration after the intervention is complete and maximizes response rates for follow-up surveys within a range supported by the published literature [41], our previous RCT [5], and our implementation trial [6]. The use of various incentives is standard in psychological research and, increasingly, in clinical trials, providing the size of the payment does not put “undue” pressure on individuals to participate, and the sample is not drawn from a “vulnerable population” [42,43]. Our survey incentives ($105 over the course of multiple surveys for a year) are well within the range considered acceptable (adjusted for inflation) by authors publishing in Contemporary Clinical Trials [44].

Every intervention arm participant who completes all 4 sessions of the IDEA^3^ program will receive a certificate of attendance for their resumé.

### Outcome Measures

#### Primary Outcomes

The primary aim of the trial is to test whether IDEA^3^ can reduce the 1-year incidence of completed rape among women attending university in Canada and the United States. Completed rape will have occurred when a participant indicates she has had at least one experience of threatened, forced, or drugged completed (not attempted) sexual activity (oral, anal, or vaginal intercourse)—answered “once” or more to any of 9 items (2c-e, 3c-e, and 4c-e) in the period between the last outcome measurement and the current day (SES-SFV). Dates of occurrences will be recorded using a calendar function to allow time-to-event analyses. The SES-SFV has been used in very large university and college and community samples and is considered the gold standard. We use the gender-specific version (male perpetrator) due to the focus of the intervention. Responses on the scale are stable across administrations [28] and are comparable to those received through interviews [45]. The validity of the scale has been demonstrated in many published studies [28,47]. Predictive validity has been demonstrated with correlations between sexual victimization and variables predicted to be influenced by it, such as trauma symptoms [28].

#### Secondary Outcomes

The secondary aim of the trial is to test the hypotheses that IDEA^3^ can reduce the 1-year incidence of: (1) attempted rape; (2) attempted or completed sexual coercion; and (3) forced sexual contact (nonpenetrative SA). Attempted rape will have occurred when a participant answered she has had at least one experience of attempted, threatened, forced, or drugged completed sexual activity (oral, anal, or vaginal intercourse)—answered “once” or more to any of 9 items on the SES-SFV (5c-e, 6c-e, 7c-e) in the same period. Sexual coercion will have occurred when a participant reports one or more incidents of verbally coerced (excluding threats of physical harm) nonconsensual oral, vaginal, or anal intercourse—answered “once” or more to any of 6 items (2a-b, 3a-b, 4a-b). Attempted sexual coercion is assessed when a participant reports that sexual coercion was attempted but did not occur—answered “once” or more any of 6 items (5a-b, 6a-b, 7a-b). Forced sexual contact will have occurred when a participant indicates she has had an experience of threatened, forced, or drug-facilitated sexual touch (excluding intercourse)—answered “once” or more to any of 3 items (1c-e). Dates of occurrences for the first reports in any period will be recorded using a calendar function to allow time-to-event analyses.

#### Tertiary Outcomes

The main tertiary aim is to test the hypothesis that IDEA^3^ can positively affect the 6 outcomes shown to be mediators of decreases in SA victimization [47]: (1) increase women’s ability to detect risk in hypothetical situations, (2) increase women’s knowledge of and willingness to use the most effective self-defense strategies, (3) increase women’s confidence that they could defend themselves if confronted with a SA situation, (4) increase women’s perception of their own risk of SA by male acquaintances, (5 and 6) reduce rape myth beliefs and woman-blame that hamper risk detection.

The expanded cognitive appraisal model [48] upon which the intervention is built proposed a process through which changes to the primary outcome of rape victimization would be accomplished. Chained mediation analysis of the original RCT data supported this theory and showed that 3 measures (risk detection, knowledge, and willingness to use effective strategies, and self-defense self-efficacy) were primary mediators that explained 95% of the decrease in completed rape and 76% of the decrease in attempted rape [47]. Other attitudes and beliefs (perceived risk of one’s own SA risk from male acquaintances, general rape myth beliefs, and belief in female precipitation of rape) were more distal mediators that led to improvements in the primary mediators. Measurement of mediators (common to the original EAAA RCT) will allow targeted revision to the IDEA^3^ program if necessary to strengthen program material meant to impact the mediators that were not significantly affected by the intervention.

Tertiary aims additionally include testing the hypothesis that IDEA^3^ can, (7) reduce women’s self-blame if a rape occurs, as previously demonstrated with the in-person version of EAAA, as well as exploratory hypotheses related to whether IDEA^3^ can, (8) reduce attitudes related to acceptance of sexualized violence using the Acceptance of Sexualized Aggression scale [33] and, (9) increase sexual empowerment, using 13 items drawn from the Sexual and Reproductive Empowerment Scale [34].

### Methods for Protecting Against Sources of Bias

#### Selection Bias

Randomizing a large number of participants is expected to minimize selection bias, that is, minimize baseline differences between the intervention and control groups. Selection bias is further minimized by concealing the random assignment to participants until they complete the baseline assessment and arrive at the virtual intervention session.

#### Outcome Assessment Bias

Blinding is not possible in this trial. However, bias in outcome assessment is minimized by having the primary outcome, SA, collected with the best measure of coercive sexual experiences available (SES-SFV) [45]. This measure will be applied equally to all study participants. The measure has been tested on tens of thousands of undergraduates, and it has high reliability and validity [28,45]. Self-report through the SES-SFV has been the gold standard for assessing SA experience, as external adjudication is not possible and allows comparison to the original RCT. The instrument follows best practice for not using terms like “sexual assault” directly but instead assessing by describing the behavior (eg, “A man put his penis into my vagina, or inserted fingers or objects without my consent by using force, for example, holding me down with his body weight, pinning my arms, or having a weapon”). This measure, therefore, avoids issues with survivors not labeling their experience as “assault” despite it meeting the definition as intended.

#### Differential Dropout

Our pilot testing prior to the original EAAA RCT indicated that dropouts are minimized by having follow-up times coincide with the school year rather than with holiday breaks. We use the same follow-up timing in this trial. As we have done previously, we use frequent reminders (sent out by RAs at each site and automated within REDCap) for those who have not responded to maximize response. For students who have not completed a 6- or 12-month follow-up survey within 2 weeks after the final reminder, we invite them to complete a shorter survey that just includes the SES-SFV (primary and secondary outcomes) at 6 months and 12 months. Taken together, these methods reduce the attrition rate considerably. There is a possibility that women in the control arm may not feel as connected to the research and drop out of the study as a result. We have reduced the likelihood of differential dropout by providing a brief intervention (consent workshop) rather than using a no-contact control, a participant kit including snacks and resources mailed to the home of control participants as well, increasing incentives and personalized email/text contact, as well as offering the opportunity for control participants to receive IDEA^3^ at the end of the trial. Recruitment materials present both intervention and control programs as valuable to participants. As evidenced by our past research, these maximize the connection to the trial to reduce or eliminate differential attrition.

#### Between-Group Contamination

While our own and others’ research show that significant contamination is not likely to occur for an intervention of this length [49], as we have done previously, we will ask all participants at 1-week, 6- and 12-month follow-up the following questions: “Do you have any friends who were assigned to the other program in this study?” If the answer is “yes,” they are asked, “Did she/they share anything with you about what they learned in their program?” or “Did you share anything that you learned in your workshop with her/them?” depending on their group assignment. An open text box asks them to enter what was shared. We will describe the amount of contamination occurring and discuss its possible influence on the findings.

#### Noncompliance and Loss to Follow-Up

Noncompliance (aka “no show”) is defined as not attending the assigned intervention after randomization. Lost to follow-up is defined as not being able to ascertain participants’ SA status at 1 year.

To minimize attrition, participants’ sessions will start close to the beginning of the term or closely following midterms (rather than during final assignment and examination season when participants have competing priorities). We will use incentives, reminder emails, and texts 1 week and 1 day prior to the first session, and reminder texts by facilitators for those in the IDEA^3^ arm for subsequent sessions. Using a similar level of incentives, we attained full EAAA attendance from more than 78% of participants in the previous RCT and over 90% in the IDEA^3^ pilot trial.

Nonresponse on follow-up surveys will be defined as refusing to complete one or more follow-up surveys. We use a number of procedures known to maximize response rates for follow-up surveys [40], such as confirmation of contact information at each follow-up and multiple reminder emails/texts. We use increasing incentives ($10 baseline, $15 1-week, $30 6-month, $40 12-month surveys) within a range supported by the published literature [41] and our previous RCT [5] and implementation trial [6] to maximize response rates. We have found that web-based surveys (with all appropriate security and privacy measures taken) improve the ease with which women can participate. The follow-up outcome surveys take less than 30 minutes to complete, which maximizes response rates [40].

### Sample Size Considerations

In calculating the sample size for the proposed trial, we used estimates of the 1-year incidences and difference in completed rape from the previous trial (9.8% control vs 5.2% EAAA=4.6% difference [5]). However, we conservatively powered the trial so we can still detect meaningful differences even if IDEA^3^ is less efficacious than in-person EAAA, that is, it achieves 80% of the previously observed difference (80% of 4.6%=3.7%). Therefore, assuming 1-year incidences of completed rape in the proposed trial of 9.8% in the control group versus 6.1% in the intervention group, a sample size of 1676 will have 80% power to detect an absolute difference of 3.7% (relative risk reduction of 37.75%) at a 2-sided 5% level of significance. As participants in the IDEA^3^ sessions will be in pairs, the sample size is further inflated by a design effect of 1.031, based on a within-pair correlation of 0.031 from the previous trial. Including an estimated maximum 10% lost-to-follow-up, a total of 1920 participants will be enrolled in the trial (1920=1676×1.031/0.90). Using estimates for the secondary outcomes from the previous trial [5] and similarly, assuming 80% efficacy compared with the in-person intervention, the proposed sample size yields 97% power for comparing 1-year differences in attempted rape (9.3% vs 4.6%), 92% power for sexual coercion (22.6% vs 16.1%), and 99% power for sexual contact (39.1% vs 28.5%). Using estimates for the tertiary outcomes from the previous trial [21] and similarly, assuming 80% less efficacy, the proposed sample size yields > 99% power for comparing 1-week postintervention group differences in risk perception (Cohen *d* 0.58), rape myths (Cohen *d*=0.48), risk detection (Cohen *d*=0.54), and self-defense self-efficacy (Cohen *d*=0.64).

### Statistical Analyses

Analyses will be performed after all participants have completed their 1-year follow-up survey. Following a modified intention-to-treat principle, a participant will be included in the analyses if they are randomized and complete one or more postrandomization surveys. The analyses will compare the incidence (ie, first occurrence) of each primary and secondary outcome between the IDEA^3^ and control groups with Kaplan-Meier failure curves (indicating the cumulative percentage of first outcomes among women in the respective groups) and log-rank tests. Participants who are lost to follow-up or drop out will have their data censored at the time of last contact. To account for the correlation between the paired observations, variance estimates will be appropriately inflated for within-pair clustering with the use of estimates of the design effect [50]. In case of baseline imbalances in participant characteristics, Cox proportional hazards regression models with a robust sandwich covariance matrix to account for the clustering will be used to compare the IDEA^3^ and control groups while controlling for the confounding factors. The literature [24,51,52] suggests that prior SA can be a modifier with respect to the effectiveness of SA resistance interventions. Therefore, intervention effects will be compared for women with and without SA histories at baseline by adding a cross-product term to the Cox regression model and testing for statistical significance. For the tertiary outcomes, which are all continuous, linear mixed models will be used to analyze the data that mirror a multilevel repeated-measures study design. A random intercept will be included in the models to account for the correlation between the paired observations, and a first-order autoregressive covariance structure will be used to characterize the interdependence of the repeated measures over time. A cross-product term between group and time will also be included in the models. Participants who are lost to follow-up or drop out can affect the validity of the group comparison if (1) the outcome is related to being lost or dropped, and (2) it is differential between groups. Therefore, baseline characteristics of women who are lost and drop out will be compared with women who complete the trial. In addition, the missing data mechanism will be formally tested [53] to determine whether it is Missing Completely at Random or missing at random. For completeness in assessing the effect of missingness, 2 additional analyses will be conducted: (1) a “per-protocol” analysis among participants who attend all sessions and respond to the 1-year SES-SFV questions; (2) multiple imputation of 5 data sets using a discriminant function for binary outcomes and Markov chain Monte Carlo for continuous outcomes, assuming the missing data mechanism is missing at random.

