### Randomization

When participants have completed their screening interview, they receive an email inviting them to complete the baseline survey (see section below on assessments for more details). The baseline survey must be completed no less than 24 hours before their first program session (or only program session for control participants). The email contains an individualized URL taking them directly to this first survey, which takes 30-45 minutes.

Randomization of the pair will occur once both participants in the pair complete their screening interview and baseline survey, and no later than 24 hours before the first (or only) session. If one member of the pair fails to complete the baseline survey, the other member of the pair will be given the choice of continuing in the study with a different partner (time permitting), rescheduling for a later intervention session, or discontinuing the research. In rare circumstances, that is, if the participant has been re-paired once or more, there is insufficient time to re-pair, or no one else is available for a new pairing, she will be individually randomized and permitted to complete the intervention by herself. Once the pair is randomized, they are sent a Zoom link for the session through REDCap. This link does not identify their random assignment. The facilitators/research assistant (RA) reveal the assignment once everyone is present in the Zoom room at the scheduled time.

The trial biostatistician is responsible for setting up the randomization protocols in REDCap. Randomization is stratified by site using permuted block sizes of 2 and 4, and participant pairs are randomized 1:1 to the IDEA^3^ program or control. Randomization occurs after baseline completion so that participation in the trial cannot be affected by knowledge of intervention assignment. The site coordinators generating the random assignment for a participant pair are not able to view the random allocation sequence.

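### As written, no planned comparison of the arms covers all randomized women: the multiple imputation meant to assess missingness inherits the modified intention-to-treat rule and omits those with no follow-up survey

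*Protocol article*

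**What the plan says.** The Statistical Analyses section of the protocol article sets one inclusion rule, under a modified intention-to-treat principle: "a participant will be included in the analyses if they are randomized and complete one or more postrandomization surveys".

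The same section describes how missingness will be examined. It opens that part with "For completeness in assessing the effect of missingness, 2 additional analyses will be conducted". The two analyses are:

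- a per-protocol "analysis among participants who attend all sessions and respond to the 1-year SES-SFV questions", which has its own, narrower set;
- "multiple imputation of 5 data sets using a discriminant function for binary outcomes and Markov chain Monte Carlo for continuous outcomes", under missing at random, with no population stated.

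Separately, "baseline characteristics of women who are lost and drop out will be compared with women who complete the trial", and the missing-data mechanism is to be tested formally. Neither of these compares outcomes between the arms.

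On what is known about each woman, the Randomization section says: "Randomization occurs after baseline completion so that participation in the trial cannot be affected by knowledge of intervention assignment". Both members of a pair must finish the baseline survey first. The Baseline Survey section lists demographics, the SES-SFV, several mediator scales and the exploratory scales.

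On dropout, the Differential Dropout section raises the possibility that "women in the control arm may not feel as connected to the research and drop out of the study as a result". It then lists countermeasures, which it expects to reduce or remove the difference.

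**The concern.** Inclusion in the analysis set depends on something that happens after randomization, namely answering at least one follow-up survey. The trial is open-label, and the arm is revealed at the first session, before any follow-up survey. Contact after that point differs: controls attend one 60-minute workshop, while IDEA3 women attend four sessions with reminders in between. Never responding could therefore differ by arm, and the article itself raises differential dropout as a possibility.

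Multiple imputation is the one planned analysis that could bring these women back, because their baseline data exist. If it is run on the modified set, it fills in later gaps for women who answered at least once and ignores those who never answered. The per-protocol analysis removes still more women. Agreement between the main result, the imputation and the per-protocol analysis would then say nothing about the never-responders, yet could be read as reassurance about missing data in general.

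**Working it through.** **1. The plan's own figures.** Sample Size Considerations gives 9.8% against 6.1%, two-sided 5%, 80% power. The pooled-variance formula for two proportions gives 838 per arm, so 1676 in all. Inflation: 1676 × 1.031 / 0.90 = 1919.95, so 1920. Both figures reproduce and are not in dispute. The 10% allowance is 192 of 1920 women. It refers to SA status not known at 1 year, so women with no survey at all are a subset of it.

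**2. Which analyses include a randomized woman with no follow-up survey?**

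| Planned analysis | Population | Included? |
|---|---|---|
| Kaplan-Meier, log-rank, Cox | general rule | no |
| Mixed models for tertiary outcomes | general rule | no |
| Per-protocol | all sessions plus 1-year SES-SFV | no |
| Multiple imputation | none stated, so general rule | no, by inference |
| Baseline comparison of lost women and completers | lost women and completers | yes, but not a comparison of the arms |

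In the log-rank analysis her exclusion costs nothing. With no follow-up she would be censored at time zero and would enter no risk set.

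**3. How far could the analysed difference move?** The share of never-responders and their risk are not in the documents. Both are assumed here, within the 10% allowance.

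*Scenario A: more controls never respond.* Let p be the true risk in an arm, m the share never responding, and k their risk relative to the arm's average. The risk among the women analysed is p(1 − mk)/(1 − m). Take p = 9.8%, m = 5% in controls (48 of 960) and p = 6.1%, m = 2% in IDEA3 (about 19 of 960).

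- k = 2: control 9.8 × 0.90/0.95 = 9.28%; IDEA3 6.1 × 0.96/0.98 = 5.98%; difference 3.31 points.
- k = 3: control 9.8 × 0.85/0.95 = 8.77%; IDEA3 6.1 × 0.94/0.98 = 5.85%; difference 2.92 points.

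The true difference is 3.7, so the analysed effect is too small.

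*Scenario B: the women analysed have 9.8% and 6.1%, and the risk in all randomized women is rebuilt* as (1 − m) × analysed risk + m × risk in never-responders.

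- m = 5% in both arms, never-responders at 9.8%: IDEA3 0.95 × 6.1 + 0.05 × 9.8 = 6.285%; difference 3.52.
- m = 10% in both arms, never-responders at 9.8%: IDEA3 0.90 × 6.1 + 0.10 × 9.8 = 6.47%; difference 3.33.
- m = 5% in controls and 10% in IDEA3, never-responders at 15%: control 0.95 × 9.8 + 0.05 × 15 = 10.06%; IDEA3 0.90 × 6.1 + 0.10 × 15 = 6.99%; difference 3.07.

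Here the analysed 3.70 is too large. The two scenarios point in opposite directions.

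**4. What would imputing these women recover?** In scenario A with k = 2, suppose baseline variables explain none of the doubled risk. Imputation under missing at random then gives never-responders about the analysed risks, and the difference stays near 3.31. If baseline variables explain all of it, the difference returns towards 3.7. Recovery lies between the two.

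**The case against.** The strongest objection is that the article never states the imputation population. The inclusion rule is followed at once by the description of the incidence comparison, the imputation comes later as an additional analysis, and the per-protocol analysis shows that the general rule does not define every population. The SAP, which is not shown, may set it. This stands in part: exclusion from the imputation is inferred, not stated. But the rule is worded for the analyses as a whole, and the only analysis given a different set is narrower still. An SAP that followed the article would leave these women out.

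Several stronger readings are tempting, and the documents do not support them.

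- *That these women are dropped from every analysis.* They belong to the lost women in the baseline attrition comparison. What is missing is a comparison of the arms that includes them.
- *That the primary analysis is damaged by the rule.* The log-rank test would be the same with them in.
- *That each exclusion happens with the arm known.* The session link does not show the assignment, so a woman who misses the first session and never responds may not have learned it.
- *That differential non-response is to be expected.* The article calls it a possibility and names countermeasures. These include a short SES-SFV-only survey at 6 and 12 months, which should shrink the no-survey group.
- *That baseline data are complete for all.* The survey must be completed, but single items may be blank, and risk detection and resistance knowledge are first measured after the intervention.
- *That the fix would recover the whole 0.4 to 0.8 points of scenario A.* It would not, unless baseline variables explain the excess risk.

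**Conclusion.** The point holds in a limited form. The stated rule, read plainly, leaves no comparison of the arms that covers all randomized women, and the imputation intended to assess missingness omits those with the most complete missingness. That is more than absent detail, because a stated rule produces it.

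Neither the size nor the direction of any bias can be established from the documents. Under the assumed shares and risks above, a true 3.7 points would be seen as 3.3 to 2.9, or an analysed 3.7 would stand for 3.52 to 3.07 among all randomized women. If almost everyone answers at least one survey, the effect is negligible. This is an inexpensive improvement to a supplementary analysis and not a flaw in the primary test.

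**What to change.** Keep the modified set for the Kaplan-Meier and log-rank analysis. State in the SAP that the multiple imputation is run on all randomized women, with arm, site, baseline SES-SFV history and the other baseline measures as predictors. Report by arm the number of women with no post-randomization survey. Add that, under missing at random, this analysis corrects only the part of any bias that the baseline variables explain.

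The cost is a few sentences in the SAP and one line in the participant flow. No new data are needed and the primary analysis does not change. Data collection runs to May 2027, so the change can be made before any analysis.
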